***Group 2***

The vial of gold microparticles is mixed with 2 ml hyaluronic acid (Suplasyn®, 20mg/2ml**,** and the mix of gold and hyaluronic acid is injected intra-articularly into the patient’s knee.

Patients in group I for evaluation of the modulation of macrophages and mast cells. Quantitative sensory testing, patient-reported questionnaires, clinical examination, and blood and synovial samples will be collected before and 8 weeks after treatment. At the 2-year follow-up, patient-reported questionnaires and additional treatments will be collected.

Patients in group II for evaluation of the generalized effect on pain and function will be treated using gold microparticles and hyaluronic acid will be followed using patient-reported questionnaires. This group will be followed before, 8 weeks after, and at 2 years using patient-reported questionnaires, and additional treatments will be collected.

***Clinical pain and function assessment***

WOMAC Pain, function and stiffness score

The Western Ontario and McMaster Universities Arthritis Index WOMAC [6] is a subject-rated instrument that measures Osteoarthritis (OA) symptoms. The questionnaire contains 5 pain questions, 2 stiffness questions, and 17 physical function questions (24 questions total). Each question utilizes a 5-point scale, from 0 (none) to 4 (extreme). The WOMAC score will be used before treatmen and 8 weeks and 2 years after.

Weekly Pain Diary

Subjects rated their pain intensity on a VAS scale every day at home. On the VAS scale ‘‘0” indicates ‘‘no pain”, and ‘‘10” indicates ‘‘maximal pain”. Subjects rated the pain severity for Average Pain Score (APS) for the last 24 hours, worst pain for the last 24 hours, and pain severity at night. The weekly pain diary will be used for 8 weeks after treatment.

Global Rating of Change Scale

Using the Global Rating of Change Scale, we asked the question, “Concerning your knee, how will you describe yourself compared to immediately before the injection of gold into your knee” and evaluated the answer on an 11-point scale from very much worse (-5) to complete recovered (5) with a score of “0” indicating no changes. The global rating scale will be used 8 weeks and 2 years after treatment.

Pain Detect questionnaire (PDQ)

The PDQ is a validated, easy to use screening tool that predicts the likelihood of a neuropathic pain component in chronic pain disorders[14]. It shows higher sensitivity and specificity in comparison with other neuropathic pain screening questionnaires. The questionnaire is comprised of 3 major components: gradation of pain, pain course pattern and radiating pain. There are 7 questions evaluating gradation of pain. Each question is scored by the patient using a 0 to 5 score with 0 = never, 1 = hardly notice, 2 = slightly, 3 = moderately, 4 = strongly and 5 = very strongly. There is one question evaluating pain course patterns. Patients select from one of four pictures to indicate which pattern of pain best describes their course of pain. Each picture is associated with a unique score of 0, -1, or +1 (2 pictures have this score possible). There is one question evaluating radiating pain with a yes (score of +2) or no (score of 0) response option. The PD-Q is calculated by the addition of the patient’s responses to all questions. Thus, the maximum possible score is 38, the minimum possible score is -1. Only integral values are possible. Total PD‑Q scores of ≤ 12 indicate that a neuropathic pain component is unlikely (< 15%). Total PD‑Q scores of ≥ 19 indicate that a neuropathic pain component is likely (>90%). Scores of 13 to 18 are uncertain.

***Quantitative Sensory Testing (QST)***

QST will be performed before and 8 weeks after treatment

*Pressure Pain Sensitivity*

A handheld algometer (Somedic, Hörby, Sweden) with a 1-cm^2^ probe (covered by a disposable latex sheath) is used to record the pressure pain threshold (PPT) on 7 sites at the affected knee with two distant sites at the tibialis anterior muscle (TA, 5 cm distal to the tibial tuberosity) and at the extensor carpi radialis longus muscle (arm, 5 cm distal to the lateral epicondyle of humerus). The sites in the peripatellar regions will be: 2 cm distal to the inferior medial edge of patella (Site 1); 2 cm distal to the inferior lateral edge of patella (Site 2): 3 cm lateral to the midpoint of the lateral edge of patella (Site 3); 2 cm proximal to the superior lateral edge of patella (Site 4): 2 cm proximal to the superior edge of patella (Site 5); 2 cm proximal to the superior medial edge of patella (Site 6); 3 cm medial to the midpoint of the medial edge of patella (Site 7). An interval of minimum 20 seconds is kept between each PPT assessment. The PPT is defined to the subject as ‘‘the point at which the pressure sensation just becomes painful.’’ Pressure is increased gradually at a rate of 30 kPa/s until the pain threshold is reached and the subject presses a button.

*Cuff Pressure Algometry*

Deep-tissue pain sensitivity will be evaluated by cuff pressure stimuli using a computer-controlled cuff algometer (NociTech and Aalborg University, Denmark) including a 13-cm wide tourniquet cuff (VBM, Sulz, Germany) and an electronic VAS (Aalborg University, Denmark) for recording of the pain intensity. The cuff will be placed at the level of the head of the gastrocnemius muscle of the leg most affected by knee OA. The electronic continuous VAS (sliding resistor) is 10 cm long and sampled at 10 Hz; 0 cm indicated “no pain” and 10 cm indicated “maximum pain”.

The cuff is automatically inflated (inflation rate: 1 kPa/s). The subject is instructed to rate the pain intensity continuously on the VAS from the first sensation of pain (pressure detection threshold, PDT) and to press the release button at “the pain intensity strong enough to make one feel like interrupting or stopping it”. The pressure value at the termination of pressure inflation is defined as the pressure-pain tolerance (PTT) and the corresponding VAS-score is defined as the pressure-pain limit.

A total of 10 repeated mechanical pressure stimuli will be delivered at 0.5 Hz (1 s stimulus duration and 1 s interval between stimuli) to the lower leg to evaluate temporal summation. A constant pressure between the individual pressure stimuli of 1 kPa will be applied to avoid movement of the cuff. During the 10 repeated stimuli, the patients will be instructed to continuously rate the pain intensity on a 10 cm continuous VAS (sliding resistor) (“0” represented “no pain”, and “10” represented “maximal pain”).

A painful conditioned stimulus will be applied to the contralateral lower leg simultaneously; assessment of PDT and PTT will be performed using a single chamber cuff on the ipsilateral lower leg (test stimulus) as a measure of CPM. The conditioned stimulus will be terminated right after the PDT and PTT are assessed.

**Sample collection and biobanking**

SF from the knees will be centrifugated for 10 minutes at 2200G to remove cell debris, and the supernatant frozen in aliquots at -80℃ for future analysis. Besides, a 6 ml venous whole blood sample was taken and centrifugated at 3000 RPM for 15 minutes. The serum fraction will be stored at -80℃ for future analysis. All sample data will be collected and kept following Danish legislation on data handling at the Department of Biomedicine at Aalborg University Hospital. Each patient sample will be divided into aliquots to avoid unnecessary freezing and thawing cycles.

Cell free DNA will be determined in SF and serum by Quant-iT™ PicoGreen™ dsDNA Assay Kit (ThermoFisher Scientific) according to the manufacture’s instruction (Birkelund et al., 2020). A Proximity Extension Assay (PEA) will be carried out essentially according to Giordano et 2020 on representative SF samples (n=6) to quantify low abundance affected by the gold treatment essentially. Sample preparation for proteome analysis will be prepared essentially as Birkelund (Birkelund et al., 2020). The protein concentration in biofluids will be measured by a microassay. A total of 25ug SF and serum subject to in-situ trypsinization (trypsin ratio 1:100) using reduction and alkylation using a Filter Aided Sample Preparation protocol (10kDa cut-off) before analysis with tandem mass spectrometry (MS/MS). To expand the protein coverage of the MS analysis, a pH-fractioning of the enzymatically digested samples will be carried out. A total of 500ng tryptic digest will be analyzed in technical duplicates in randomized order using a nano UPLC ESI MS/MS setup consisting of a Dionex RSLC nano pump (Dionex RSLC, Thermo Fisher Scientific) connected to a Bruker timsTOF PRO mass spectrometer operated in DIA-PASEF positive ion mode (Bruker Daltronics, DE).

*Proteomic measures*

The analyses of the proteomic primary raw data output will be searched against spectral databases generated by fractionated pooled samples using human reference proteome database (05.2021; 20364 entries) in Biognosys Spectronaut (v. 14.10) and using statistical analysis. Quantitative proteome analysis of SF and serum samples will be accomplished by discovery proteomics using DIA-PASEF. Functional association of significantly regulated proteins in SF and serum with gene onthology and function will be assessed by Metascape

**Procedure**

After signing the informed consent patients will be investigated clinically and included/excluded according to the criteria. If included, they are invited back to the clinic. The clinical and experimental measures will be assessed at baseline. The patients will receive the intraarticular gold injection in the affected study knee. Patients will come back to the clinic after 8 weeks where all the measures will be taken. During the 8 weeks period the patients will fill in the daily pain diary and medication used. Patients will come back for a 2-year follow measuring clinical pain and function.

**Risks, side effects and disadvantages**

The pain assessment methods used are well-proven and all are performed in accordance with standard procedures previously used in similar studies. There are no reports from our or other institutions on long-term side effects of the methods. The applied stimulation can be interrupted at any time. The subjects will be under observation during the trial.

Patients will experience weak and short-term pain during quantitative sensory testing (QST). Specifically, the pressure stimulation will cause a pressing or clamping pain however, the pain disappears immediately after the end of the influences and does not cause any side effects.

Intraarticular injection of the small volume of gold particles are not expected to give any residual side effects as intraarticular injection is a standard clinical procedure. Patients may experience some pain associated with the injection, which is a normal reaction. The injection site is properly sterilized according to the clinical standard to minimize the possibility of inducing an infection.

Injection of gold is used in different settings for treatment of articular pain.

**Study shortcomings**

The study is not investigating the effect of the gold injection as such but the possible role of modulating specific inflammatory mechanisms, pain, and function. Therefore, the study is not including a placebo control.

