**Study goals and objectives**

The purpose of this study is to investigate if specific effects can be obtained by modulating selectively macrophages and mast cells in the osteoarthritic knee joint as assessed by mechanistic pain assessment tools (quantitative sensory testing), blood and synovial fluid analysis, and clinical pain ratings in patients with painful knee osteoarthritis.

Hypothesis: Modulating macrophages and mast cells by gold microparticles injected into the osteoarthritic knee joint will modulate inflammation specifically, inhibit pain sensitisation and provide pain relief to patients with knee OA.

The aim of this study is to use gold particles as a model compound to modulate specifically and selectively the function of macrophages and mast cells and investigate how this modulates pain and pain sensitization, clinical outcome, and proteomic markers in synovial fluid and serum.

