**Study design**

**Patients**

***Group 1***

For this part of the study 30 patients with single knee OA will be included using a narrow set of inclusion and exclusion criteria for evaluation of the modulation of macrophages and mast cells.

The following inclusion and exclusion criteria will be used.

Patients with radiographically confirmed KOA (Kellgren-Lawrence grade ≥ 2), pain for more than three months, and maximal pain intensity VAS (Visual Analogue Scale, 0-10) ≥ 5 during the last week, and with knee joint effusion on MRI that can be aspirated. Eligible patients were enrolled at the specialized, public outpatient clinic at Aalborg University Hospital, Denmark. The exclusion criteria were: 1) active adjuvant treatment for any malignancy, 2) active infection and antibiotic treatment, 3) active treatment with steroids, biological or other anti-rheumatic medication, 4) chronic pain and other than knee joint pain, 5) inability to comply with the protocol and, 6) inadequacy in written and spoken national language.

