***Group 1***

5-10 ml of synovial fluid is aspirated (20G needle) from the affected OA knee. The vial of gold microparticles is mixed with 2 ml synovial fluid**,** and the mix of gold and synovial fluid is injected intra-articularly into the patient’s knee. The remaining synovial fluid and additional blood samples are collected and stored for future analysis.

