**Statistical analysis**

This present exploratory study will investigate whether gold ions have a clinical role in treating KOA. Based on preclinical evidence, we estimated medium effect size (Cohen’s d = 0.5), and with a power of 80% and a significant level at 0.05, a sample size calculation estimated a total sample of 27 subjects will be needed in group 1. A total of 30 subjects will be included to account for possible drop-out.

The clinical outcome measures analysis will be performed using the Stata software, version 16.0 (StataCorp.) ANOVA will be used for the analysis of repeated measures of pain, the pain diary, and QST parameters. Wilcoxon test will be used for all other measurements.

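### The protocol excuses the missing control by saying the effect of gold is not under study, yet its hypothesis, expected outcome and sample size rest on that effect; before-after change in Group 1 cannot be attributed to gold

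*Protocol*

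**What the plan says.** All references are to the protocol.

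- **Study shortcomings**: "The study is not investigating the effect of the gold injection as such". The rest of that sentence names inflammatory mechanisms, pain and function as the subject instead, and the sentence after it draws the consequence: "Therefore, the study is not including a placebo control".
- **Study goals and objectives**, hypothesis: gold microparticles injected into the knee "will modulate inflammation specifically, inhibit pain sensitisation and provide pain relief to patients with knee OA".
- **Statistical analysis**: "This present exploratory study will investigate whether gold ions have a clinical role in treating KOA". Group 1 is sized there on Cohen's d = 0.5, 80% power and a 0.05 level, giving 27, raised to 30 for drop-out. No outcome is named for d, and the sidedness of the test is not stated.
- **Project summary, Expected outcome**: a 0.5 SD difference is expected in the primary outcome, WOMAC, and more than 70% of all patients are expected to report that the treatment helped. No comparator is named for either.
- **Study design, Group 1**: entry requires maximal VAS pain of 5 or more in the last week and an effusion, "with knee joint effusion on MRI that can be aspirated".
- **Methodology, Group 1**: "5-10 ml of synovial fluid is aspirated (20G needle) from the affected OA knee", of which 2 ml is mixed with the gold and returned. Measurements are taken before treatment and at 8 weeks, with questionnaires again at 2 years.
- **Methodology, Group 2**: gold is carried in hyaluronic acid, in a differently selected population.

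**The concern.** The reason given for having no control does not agree with what the protocol sets out to learn. If pain relief from injected gold is the hypothesis, the effect of the injection is under study. Recasting the aim as mechanism does not remove the difficulty: to say that gold modulates macrophages and mast cells, and thereby pain, is still a causal statement about the injection. The Study shortcomings sentence itself keeps pain and function among its targets.

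The planned comparison answers another question. Its null hypothesis is no change over 8 weeks, not no effect of gold. The protocol's own text supplies reasons to expect change with inert gold: selection on recent high pain and an effusion, removal of joint fluid, and self-reported scores with no blinding described. The global rating question even names the gold injection. At stake is the main conclusion. A significant fall in WOMAC could be reported as pain relief from gold, and no section of the protocol limits that attribution.

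**Working it through.** **1. Which test does the stated sample size match?**
Inputs from Statistical analysis: d = 0.5, power 80%, level 0.05. For a paired t test of mean change against zero, power comes from the noncentral t distribution with n − 1 degrees of freedom and noncentrality d√n; at n = 27 this is 0.5 × √27 = 2.60.

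| Form | n needed |
|---|---|
| Paired, one-sided 5% | 27 (power 81.2%) |
| Paired, two-sided 5% | 34 (power 70.6% at 27, 75.4% at 30) |
| Repeated-measures ANOVA, f = 0.25, correlation 0.5 assumed | 34 (2 times), 28 (3 times) |
| Two independent groups, normal approximation | 50 per arm one-sided, 63 two-sided |

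Of the forms tried, only the one-sided paired test gives 27 exactly. The figure belongs to a before-after comparison and not to a between-group one.

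**2. Is there a comparator elsewhere?**
Group 2 differs in selection (Kellgren-Lawrence grade 1 allowed, multisite pain allowed, no effusion required) and in carrier, and it also receives gold. It cannot stand in for a control.

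**3. Fluid removed.**
Group 1 has 5 to 10 ml withdrawn and 2 ml returned: a net 5 − 2 = 3 ml to 10 − 2 = 8 ml.

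**4. How large could regression to the mean be in the entry measure?**
The documents give no distribution, so these inputs are assumed: normal scores, an entry cut-off at the clinic mean or 0.5 SD below it, and a repeat correlation r of 0.6 to 0.8. With the cut-off a in SD units:

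- mean of the selected patients above the clinic mean: λ = φ(a)/(1 − Φ(a)), which is 0.798 for a = 0 and 0.509 for a = −0.5;
- expected fall: (1 − r)λ, in SDs of the entry score;
- variance of change: (1 − r)²(1 + aλ − λ²) + (1 − r²).

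| a | r | Fall, SD of entry score | SD of change | Fall, SD of change |
|---|---|---|---|---|
| 0 | 0.6 | 0.4 × 0.798 = 0.32 | √(0.16 × 0.363 + 0.64) = 0.84 | 0.38 |
| 0 | 0.8 | 0.2 × 0.798 = 0.16 | √(0.04 × 0.363 + 0.36) = 0.61 | 0.26 |
| −0.5 | 0.6 | 0.4 × 0.509 = 0.20 | √(0.16 × 0.486 + 0.64) = 0.85 | 0.24 |
| −0.5 | 0.8 | 0.2 × 0.509 = 0.10 | √(0.04 × 0.486 + 0.36) = 0.62 | 0.17 |

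The paired test works in SDs of change, so the relevant range is 0.17 to 0.38. It applies to the entry VAS. WOMAC shares only part of it, and the Procedure section places baseline at a later visit, by which time some regression will already have occurred.

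**5. What does the test do if gold is inert?**
Suppose all causes other than gold together produce the change shown (assumed, in SDs of change). The probability of a significant result at n = 27 to 30 is:

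| Non-gold change | Two-sided 5% | One-sided 5% |
|---|---|---|
| 0 | 5% | 5% |
| 0.3 | 32-36% | 45-48% |
| 0.4 | 52-56% | 65-69% |

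**The case against.** The study calls itself exploratory, presents gold as a model compound for probing macrophages and mast cells, and declares the missing placebo under a heading about shortcomings. On that view, not studying the injection as such means studying mechanism rather than efficacy, and a single-group design is a legitimate exploratory choice. The test against zero is nowhere written, the inputs in steps 4 and 5 are assumed, and the laboratory measures are not self-report.

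Much of this stands. A reader might infer that the protocol asserts a clinical role for gold. It does not: the Statistical analysis section says only that the question will be investigated, and pain relief is stated as a hypothesis, not a conclusion. A reader might also infer that the missing control is concealed, or that a single-group design is in itself an error; the first is untrue, and the second does not follow for exploratory work. The test against zero is inferred from the one-group design and the match to 27.

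What does not stand is the mechanistic reading as a defence. The hypothesis includes pain relief, the primary outcome is WOMAC, and the summary expects most patients to report benefit. Disclosing the gap with a reason that other sections contradict does not limit the conclusion. Laboratory measures escape expectation, but they too are compared only before and after.

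**Conclusion.** The concern holds as an inconsistency in the current text with a consequence for inference. The ground given for omitting a control conflicts with the hypothesis, the expected outcome and the basis of the sample size, and the before-after comparison in Group 1 cannot attribute change to gold. That conclusion follows from the design and needs no assumed figure.

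The size is illustrative. Selection alone could give about 0.17 to 0.38 SD of change in the entry measure, and less in WOMAC. A total non-gold change of 0.3 to 0.4 SD would make an inert treatment significant in roughly a third to just over half of trials two-sided, and in 45% to 69% one-sided. These are not predictions of this trial's error rate; they rest on an assumed cut-off position, correlation and total.

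Two stronger inferences are not supported. The documents do not show that gold is ineffective. Nor is 27 arithmetically wrong: it is reproducible, but only with a one-sided test that the protocol does not state.

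**What to change.** Reconcile the Expected outcome, Study goals and objectives, Study shortcomings and Statistical analysis sections together; changing only some of them leaves the contradiction in place.

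1. Restate the aim and hypothesis, including the mechanistic and biomarker aims, as estimating within-patient change from baseline to 8 weeks after the whole procedure as the protocol describes it: for Group 1, aspiration plus gold in synovial fluid; for Group 2, gold in hyaluronic acid. Apply the measures each group actually has.
2. In Expected outcome, present the 0.5 SD and the 70% as expected change and expected patient report, not as benefit caused by gold.
3. In Study shortcomings, replace the present reasoning with a statement that, because there is no concurrent control, change will not be attributed to gold and no efficacy conclusion will be drawn.
4. Optionally, show change in knee PPT minus change in arm PPT as a supplementary contrast beside the raw changes. State its limits: it removes only retest drift and general response shifts, it does not address aspiration, regression in the selected knee or expectation directed at the knee, it does nothing for WOMAC, and it may subtract a true central effect.

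Replacing the test with a 95% confidence interval would not be enough, since an interval that excludes zero is the same two-sided test.

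Cost: wording in four sections, plus one optional contrast from data already collected. Design, sample size and procedures are unchanged.
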